### Interim analyses {21b}

The interim analysis is deemed unnecessary for this study, given follow-up conditions: (1) short-term study period with only 3-month follow-up for each participant and risk of type I error of interim analysis and (2) a relatively small sample size of 120 patients and blinded setting of study design.

### Methods for additional analyses (e.g., subgroup analyses) {20b}

Further sensitivity analysis to assess the outcome consistency will be performed in multiple subgroups, such as according to age, sex, baseline office SBP level, implementation sites, history of diabetes or hyperlipidemia at randomization, and proportion of donor microbiota engraftment.

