### Interventions

#### Explanation for the choice of comparators {6b}

According to the “2010 Chinese Guidelines for Prevention and Treatment of Hypertension”, lifestyle intervention is recommended as the first-line therapy for grade one hypertension treatment, and pharmacological interventions can be initiated after 3 months of lifestyle intervention and persistent hypertension. All participants in this study will be educated regarding lifestyle intervention and randomized to the “FMT capsule” intervention or the “placebo capsule” intervention. Participants in the “placebo capsule” group will take placebo capsules orally on day 1, day 7 (± 1 day), and day 14 (± 1 day). The placebo capsules have identically appearing powder that does not contain donor stool or any active drug.

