#### Strategies to improve adherence to interventions {11c}

Before inclusion, the willingness to comply will be repeatedly confirmed among potential participants. An advantage in regard to compliance is that all capsules are taken at three intervention visits within two weeks. The FMT capsules and placebo capsules will be stored, delivered, and recovered by investigators and/or patient care providers from the implementation centers. All capsules will be stored in − 80 °C freezers and delivered from the trial center into implementation centers via dry ice. Before the intervention, the investigators and/or patient care providers will recover capsules in a 37 °C water bath and make detailed records of the number of distributed, administered, and returned capsules. All recovered capsules at each visit will be orally taken within 30 min under clinical supervision. The remaining study capsules will be returned to the responsible center. The participant compliance rate will be evaluated as the actual number of capsules used divided by the anticipated number of capsules used × 100%. Good compliance is defined as a compliance rate of 80–120%; poor compliance is defined as a compliance rate less than 80% or more than 120%. If poor compliance is identified, thorough communication between investigators and patients will be performed to reach possible solutions. In addition, an assessment of the gut microbial composition between FMT capsules and stool samples from recipients at different time points will be performed to assess the engraftment of microbiota, which will provide additional information regarding participant adherence in part.

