### Outcomes {12}

Our primary hypothesis is a BP-lowering effect of gut microbiota restoration via FMT compared to the effects observed in the placebo group in grade one hypertensive patients. Accordingly, the primary outcome is defined as the change in office systolic blood pressure (SBP) level from baseline to the one-month follow-up (day 30).

Other indicators related to BP evaluation, safety concerns, and potential mechanism exploration will be assessed as the main secondary outcomes and include the following:

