#### Sample size {14}

Sample size calculation was performed via PASS version 15 software before trial initiation based on the following: (1) no relevant current data for the effect of FMT on hypertension; (2) a clinically significant improvement of a decrease in office SBP at least 5 mmHg associated with reduction in stroke (14%), cardiovascular disease (9%), and mortality (7%) [32]; (3) meta-analysis of the effectiveness of probiotics on hypertension based on randomized controlled clinical trials that revealed a reduction of SBP of 3.56 mmHg (95% CI, 6.46 to 0.66) [33]. Assuming a true SBP difference between the “FMT capsule group” and “placebo group” with a mean of 5 mmHg and a standard deviation of 8.6 mmHg for SBP change per arm, a sample size of 96 grade one hypertensive patients yields > 80% statistical power to demonstrate a > 5 mmHg difference between arms at a 1-sided alpha level of 0.025. Given the potential for premature withdrawal or failure before the primary end point data were collected, a 20% rate of loss-of-follow-up was considered, resulting in 120 participants with grade one hypertension according to the “2010 Chinese Guidelines for Prevention and Treatment of Hypertension” [28]. Participants were recruited and randomized 1:1 to receive FMT by capsule or placebo capsules.

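### Donor engraftment is listed with baseline factors as a subgroup for outcome consistency, but it is a post-randomisation variable affected by treatment and cannot give a randomised FMT-versus-placebo comparison

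*Protocol article*

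**What the plan says.** Protocol article, Methods for additional analyses {20b}: "Further sensitivity analysis to assess the outcome consistency will be performed in multiple subgroups". The examples given are age, sex, baseline office SBP, site, and "history of diabetes or hyperlipidemia at randomization, and proportion of donor microbiota engraftment". Engraftment gets no separate treatment: the section does not restrict it to one arm or label it non-randomised.

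Other sections show what kind of variable it is:

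- **Outcomes {12}** lists durability of engraftment after FMT as a secondary outcome. It is judged by how similar the donor's and recipient's fecal microbiota are at days 7, 14, 30, 60 and 90.
- **Strategies to improve adherence {11c}** states that an "assessment of the gut microbial composition between FMT capsules and stool samples from recipients at different time points will be performed", partly as information on adherence.
- **Explanation for the choice of comparators {6b}** says the placebo powder "does not contain donor stool or any active drug".
- **Participant timeline {13}**, Table 1, puts allocation at day 0 and the first dose at day 1.
- **Outcomes {12}** sets the primary outcome as the change in office SBP from baseline to day 30.

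**The concern.** A subgroup analysis of a randomised trial is interpretable because, within each level of a factor fixed beforehand, the arms are still comparable by randomisation. Engraftment does not meet that condition. It arises after allocation, and FMT is meant to change it. Patients who engraft well may differ from those who do not in diet, starting flora, antibiotic exposure or adherence, and any of these may also bear on blood pressure.

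If the list is followed as written, an apparent benefit confined to good engrafters could appear with no FMT effect. A uniform effect could equally look as if it depended on engraftment. The Objectives {7} ask whether BP changes are associated with microbiome changes, so a result of this kind would attract attention. Presenting it as a check on outcome consistency would give it more authority than its design allows.

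**Working it through.** **1. Is each listed factor fixed at randomisation?** Age, sex, baseline SBP, site, and history of diabetes or hyperlipidemia: yes. Engraftment: no. Its first measurement is at day 7, after allocation (day 0) and the first dose (day 1). Its day-60 and day-90 values also come after the day-30 primary outcome.

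**2. Can any coding rescue the comparison?**

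- *Placebo coded as zero engraftment.* No positive level of engraftment contains placebo patients, so there is no between-arm contrast there.
- *FMT patients split by engraftment, each part compared with all placebo patients.* A selected group is set against an unselected one.
- *Placebo patients scored for similarity to reference donors.* Both arms then have a value, but treatment moves it, so FMT and placebo patients with the same score are not exchangeable.

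None gives a randomised subgroup effect. This conclusion needs no numerical assumption.

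**3. The plan's own figures, as background.** Sample size {14} assumes a true difference "with a mean of 5 mmHg and a standard deviation of 8.6 mmHg for SBP change per arm", at one-sided alpha 0.025, and states that "a sample size of 96 grade one hypertensive patients yields > 80% statistical power".

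- n per arm = 2 × (1.960 + 0.842)² × 8.6² / 5² = 46.4, rounded up to 47 (94 in total, against 96 stated).
- Power at 48 per arm: 81.3% by the normal approximation, 80.5% by the noncentral t.
- 96 / (1 − 0.20) = 120.

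These figures reproduce, and the point does not depend on them.

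**4. How large could the distortion be?** Assume that FMT has no effect, that engraftment and untreated SBP change are bivariate normal with correlation of size ρ (better engraftment going with a larger fall), and that the FMT arm is split at median engraftment. The better half then differs from placebo on average by

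ρ × √(2/π) × 8.6 = ρ × 6.86 mmHg.

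| Assumed ρ | Better half vs placebo, no FMT effect |
|---|---|
| 0 | 0 mmHg |
| 0.2 | 1.37 mmHg |
| 0.3 | 2.06 mmHg |
| 0.4 | 2.74 mmHg |

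A simulation (4,000 runs, 48 per arm) agrees: 1.32 mmHg at ρ = 0.2 and 2.00 mmHg at ρ = 0.3. A nominal two-sided 5% test of the better half against all placebo patients rejected in 5.4%, 8.8% and 15.1% of runs at ρ = 0, 0.2 and 0.3. With a uniform true effect of 5 mmHg and ρ = 0.3, the two halves showed reductions of 7.0 and 3.0 mmHg, which is heterogeneity that does not exist.

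**5. Within the FMT arm.** The gap between halves is twice the table value: 0 to 5.5 mmHg for ρ from 0 to 0.4. It affects any within-arm association equally, before adjustment. It is therefore a reason to label that association as confounded, not a reason for preferring it to the subgroup analysis.

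**The case against.** Engraftment is one example in an open-ended list of additional analyses. The article does not say that FMT patients chosen by engraftment will be set against all placebo patients. Defining engraftment as following FMT is compatible with an analysis confined to the FMT arm, and how strata are formed may be left to an analysis plan that is not shown. The protocol also limits the obvious confounders: recent antibiotic or probiotic use is excluded {10}, diet is to stay unchanged and is recorded {11d}, and capsules are swallowed under supervision {11c}. Finally, no document gives a value for ρ.

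Much of this stands, and it limits what can be claimed. A reader might infer that the biased comparison with all placebo patients is definitely planned; the text does not say so. A reader might also infer that placebo patients cannot be given any value. That goes too far: the Final visit (day 90) section speaks of analysing colonization after either capsule type, and similarity to a donor can be computed for anyone. The sound objection is that the value is post-treatment. The protections reduce confounding but do not remove it.

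The objection does not explain the placement. The article itself names engraftment as a subgroup factor for outcome consistency, beside baseline variables and without qualification. That is a stated choice, not detail left for later.

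**Conclusion.** The point holds at moderate severity. Engraftment should not be in the {20b} list, because no way of forming the subgroups gives a randomised FMT-versus-placebo contrast. That conclusion rests only on the timing of the measurement, its dependence on treatment and the placebo content, all of which the article states.

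The size is illustrative: 0 to 2.7 mmHg of spurious benefit for the better-engrafting half against placebo, for an assumed ρ of 0 to 0.4, SD 8.6 mmHg, normality and a median split. At ρ = 0 there is no bias. This is not an estimate of the bias in this trial.

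A reader might infer that the trial's main conclusion is at risk. The documents do not support that. The primary analysis {20a} is an intention-to-treat analysis of covariance adjusted for baseline SBP and centre; it does not use engraftment, and neither its alpha nor the sample size changes.

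**What to change.** Remove engraftment from the {20b} subgroup list and keep only variables fixed at randomisation.

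Report engraftment separately, as an exploratory and non-randomised association within the FMT arm:

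- for the day-30 outcome, use engraftment measured no later than day 30;
- adjust for baseline SBP, centre, baseline microbiota, and the recorded diet, compliance and antibiotic use;
- make no subgroup treatment-effect claim, and state that residual confounding remains.

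The cost is a change of wording and minor programming. Section {20c} says the final protocol and statistical analysis are settled before the database is locked, which leaves room for it. Table 1 already schedules the stool samples needed, at baseline and follow-up in both arms, so no new sampling is required. Under Trial status, follow-up is only expected to finish by December 2021, so the samples should be described as scheduled, not as all collected. The sample size stays at 96 evaluable and 120 recruited. The drawback is a weaker mechanistic statement.

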### Methods in analysis to handle protocol non-adherence and any statistical methods to handle missing data {20c}

A per-protocol analysis will also be performed and will include randomized patients successfully treated and exclude those presenting with major deviations (i.e., violation of core inclusion and/or exclusion criteria, use of forbidden drugs, intervention protocol violation). In terms of missing data handling, the multiple imputation method will be used for the primary endpoint. Additional sensitivity analyses will be performed with the data using the last-observation-carried-forward (LOCF) method and for the complete dataset excluding missing data. For secondary endpoints, missing data will not be handled because of the exploratory nature of the analysis.

The final protocol for the study and statistical analysis will be identified before locking the EDC database, and the *ClinicalTrials* website will be updated. Additionally, the full protocol, deidentified participant-level dataset, and statistical code will be shared along with the publication according to the journal requirements.

### Oversight and monitoring

#### Composition of the coordinating center and trial steering committee {5d}

The overall study was coordinated and overseen by the Collaborating Office and the Quality Control Committee following Good Clinical Practice (GCP) principles with online catch-up meetings every week. Additionally, the web-based EDC system allows for real-time monitoring, and scanned CRFs and examination reports will be rechecked by staff. Each implementation center will also organize a local investigation team including the local principal investigator ensuring study protocol implementation and quality control; trained investigators and/or patient care providers for participant screening, recruitment, follow-up, and adverse event handling; and staff for data collection and storage and specimen collection, processing, and storage.

#### Composition of the data monitoring committee, its role, and reporting structure {21a}

To monitor the trial process and participant safety, the data and safety monitoring committee was established, including experts of hypertension diagnosis, management, biostatistics, and other necessary fields, in reference to the STEP trial [34]; all personnel were completely independent from the funders and any competing interests. The staff of the Collaborating Office and a third party from the Medical Research & Biometrics Center, National Center for Cardiovascular Diseases, Fuwai Hospital Chinese Academy of Medical Sciences, were invited for data monitoring with periodical reports to the data and safety monitoring committee. Data and safety monitoring committee meetings will occur with onsite visits once at each site every 3 months to conduct process evaluation, participant safety monitoring, and recommendation to the trial steering committee in terms of protocol change, process continuation, and others. Of note, decisions are only made by the steering committee.

#### Adverse event reporting and harms {22}

Potential risks for FMT include transmission of currently unknown infectious agents or diseases related to donor gut microbiota, although a profound screening process was performed according to the current consensus. Other previously reported adverse events generally have mild and mainly self-limiting safety concerns (minor adverse events), such as abdominal discomfort, altered bowl habits, bloating, nausea, vomiting, flatulence, transient low-grade fever, and borborygmus, particularly in the FMT route via oral capsules [35]. Adverse events, as one of the secondary outcomes in the study, are identified as any discomfort or clinical symptoms within the study period. In addition to adverse events specifically queried by physicians at each follow-up visit, adverse events are evaluated at onset, for instance, according to the complaints by the participants or observations by the study staff. Beginning with the first intervention, all adverse events will be recorded on the AE page of the CRF and EDC system with details of onset date and time, severity, procedures, correlation, and influence on study interventions, prognosis, and date. The severity of AEs and their correlation with study interventions will be assessed according to the Common Terminology Criteria for Adverse Events (CTCAE Version 4.03, http://evs.nci.nih.gov/ftp1/CTCAE/CTCAE_4.03_2010-06-14_QuickReference_8.5x11.pdf) with a five-grade scale. Severe adverse events (SAEs) are defined as events leading to mortality, need for or prolongation of hospitalization, persistent or severe morbidity, and/or medical emergency determined by investigators in accordance with the GCP. Investigators will deal with and report SAEs to the local ethics committee immediately and to the responsible center and principal investigator within 24 h. Documented AEs will be evaluated by the staff from the Collaborating Office and a third party from the Medical Research & Biometrics Center, National Center for Cardiovascular Diseases, Fuwai Hospital Chinese Academy of Medical Sciences, within 3 days after each visit and reported to the data safety and monitoring committee in 3-month intervals. All adverse events will be reported in the trial publication.

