#### Relevant concomitant care permitted or prohibited during the trial {11d}

In reference to the hypertension guidelines, lifestyle modifications are recommended for all hypertensive patients and for all participants recruited in this study. During the treatment and follow-up period, participants will be asked to maintain a routine pattern of daily activities, such as physical activity, lifestyle, and habits. To minimize the interference caused by dietary environmental factors on the intestinal flora, recruited participants in each arm will be required to record their dietary history before each study visit and to make no dietary habit changes throughout the trial. Antihypertension medications and the use of probiotics, prebiotics, or antibiotics will be avoided during the study period except for in specific clinical conditions (i.e., persistent BP elevation over 180/110 mmHg) requiring pharmacological interventions on the basis of the physician’s evaluation. The conventional treatment for accompanying diseases in participants can remain unchanged and will be recorded. Treatment for adverse events is permitted and will be recorded.

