**Assessments**								
***Comorbid diseases and treatment***	✓							
***Physical examination***	✓							✓
***Office BP and heart rate***	✓			✓	✓	✓	✓	✓
***24-h ABPM***	✓					✓		✓
***Blood routine***	✓							✓
***Urine routine***	✓							✓
***Blood chemical test***	✓							✓
***Urine microalbumin, creatinine***	✓							✓
***ECG***	✓							✓
***Arterial stiffness (ABI, PWV)***	✓							✓
***Diet records***			✓	✓	✓	✓	✓	✓
***Patient compliance***			✓	✓	✓			
***Adverse events***			✓	✓	✓	✓	✓	✓
***Combined medications for accompanied diseases***			✓	✓	✓	✓	✓	✓
***Fecal sample collection***	✓			✓	✓	✓	✓	✓
***Blood sample collection***	✓			✓	✓	✓	✓	✓

Blood biochemical test: *ALT* alanine aminotransferase, *AST* aspartate aminotransferase, *K* potassium, *Na* sodium, *Cl* chloride, *BUN* urea nitrogen, *CREA* creatinine, *UA* uric acid, *TC* total cholesterol, *TG* triglyceride, *HDL-C* high-density lipoprotein cholesterol, *LDL-C* low-density lipoprotein cholesterol, *GLU* fasting blood glucose

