#### Final visit (day 90)

Participants will undergo a comprehensive examination to evaluate the efficacy of FMT for hypertension treatment, including physical examination, blood pressure, heart rate, 24-h ABPM, routine blood tests, routine urine tests, blood biochemical tests, urine microalbuminuria protein, creatinine, electrocardiography, and arterial stiffness assessments (ABIs, PWVs). In addition, dietary history, adverse events, and combined medications for comorbid disease will be recorded, and all CRFs will be reviewed. Additionally, effective colonization and durability of intestinal flora in hypertensive recipients after oral administration of “FMT capsules” or “placebo capsules” and the underlying mechanism of BP change and the fecal microbiota will be analyzed via metagenomic and metabolomic profiling analysis.

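### Read literally, the adverse-event definition leaves out symptom-free laboratory and ECG abnormalities that the trial collects at day 90

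*Protocol article*

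**What the plan says.** All references are to the protocol article.

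- **Definition.** The section on adverse event reporting and harms {22} says that adverse events, as a secondary outcome, "are identified as any discomfort or clinical symptoms within the study period".
- **Use.** Outcomes {12} counts the participants with an adverse event documented on the case report form. It is the only item there described as a measure of safety.
- **Detection.** Physicians ask about events at each follow-up visit. Events are also evaluated at onset, for instance "according to the complaints by the participants or observations by the study staff".
- **Grading.** "The severity of AEs and their correlation with study interventions will be assessed according to the Common Terminology Criteria for Adverse Events".
- **Tests collected.** Table 1 schedules blood routine, urine routine, blood chemistry, urine microalbumin and creatinine, and ECG at screening and day 90. Its footnote begins "Blood biochemical test: *ALT* alanine aminotransferase, *AST* aspartate aminotransferase, *K* potassium, *Na* sodium" and goes on to chloride, urea nitrogen, creatinine, uric acid, lipids and glucose. The final-visit section lists "routine blood tests, routine urine tests, blood biochemical tests, urine microalbuminuria protein, creatinine, electrocardiography" and introduces the visit thus: "Participants will undergo a comprehensive examination to evaluate the efficacy of FMT for hypertension treatment".
- **Named risk.** The harms section warns: "Potential risks for FMT include transmission of currently unknown infectious agents or diseases related to donor gut microbiota".

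**The concern.** Discomfort and clinical symptoms describe what a patient feels or presents with. A marked rise in ALT or creatinine, a change in blood count or a new ECG abnormality can occur without either. Such a finding does not meet the stated definition, so it need not enter the count that serves as the trial's safety outcome.

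The stake is safety reporting. If the arms differed in these objective findings, the adverse-event comparison need not show it. The reports to the monitoring committee are built from documented adverse events, so they would share the gap. This matters for a donor-derived product whose protocol names transmission of unknown agents as a risk, because such a harm may show in a test result before it causes symptoms. Centers that read the sentence literally and centers that read it broadly would also produce counts that are not comparable.

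**Working it through.** The plan gives no figure on this point and no arithmetic applies. The check sets the sections side by side.

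**1. Match each scheduled measurement to a listed outcome** (Table 1 and the final-visit section against Outcomes {12}).

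| Measurement | Schedule | Place among listed outcomes |
|---|---|---|
| Office BP | screening, days 7, 14, 30, 60, 90 | primary and secondary |
| 24-h ambulatory BP | screening, days 30, 90 | secondary |
| ABI, pulse wave velocity | screening, day 90 | secondary |
| Fasting glucose, lipids | screening, day 90 | secondary |
| ALT, AST, electrolytes, urea nitrogen, creatinine, uric acid | screening, day 90 | none |
| Blood routine, urine routine | screening, day 90 | none |
| ECG | screening, day 90 | none |

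The last three rows could reach a listed outcome only through the adverse-event count.

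**2. Ask whether the definition lets them in.** The sentence names discomfort and clinical symptoms. It does not mention signs or abnormal laboratory or ECG findings. A symptom-free abnormality in the last three rows does not meet it.

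**3. Ask whether neighboring text widens the definition.**
- CTCAE is cited for severity and relatedness. It is applied to events already identified as adverse events and does not decide what counts as one.
- Staff observation is a route by which events come to light. It tells staff how to find events, while the definition tells them what to look for.
- The day 90 examination is introduced as an efficacy evaluation. No step is stated by which an abnormal result becomes an adverse event.

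**4. Compare the two event definitions.** Serious events are defined by consequence, such as death, hospitalization or a medical emergency. Adverse events are defined by symptom. A symptom-free event with a serious consequence could therefore be a serious adverse event without meeting the definition of an adverse event.

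**5. Follow the reporting line.** Documented adverse events are evaluated within 3 days of each visit and go to the monitoring committee every 3 months. A finding outside the definition has no stated place in that line.

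**Result.** On a literal reading, the liver, renal, electrolyte, blood count, urine and ECG results have no stated place in either the efficacy or the safety outcomes unless symptoms accompany them.

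**The case against.** The strongest reply is that one loosely worded sentence is being made to carry too much. The sentence contains no express exclusion. The same section gives mild, short-lived fever, a measurable sign, as an example of an adverse event, and it allows events to surface through staff observation. Physiological change is among the grounds for discontinuing in {11b}. The article condenses protocol version 3.3, which is not shown, and the trial says that it follows GCP. Test reports are re-checked by staff, and a data and safety monitoring committee watches participant safety.

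Much of this stands. Four stronger readings are tempting, and the documents do not support them:

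- **That the plan restricts adverse events to symptoms only.** The word only is not in the text, and wider intent is plausible.
- **That abnormal results are lost or went unrecorded in practice.** They are collected and checked. The text cannot show what sites actually wrote on the form.
- **That dangerous BP rises escape notice.** The protocol's example of a condition that may need drugs is "persistent BP elevation over 180/110 mmHg". But office BP is compared by arm at every follow-up visit, and non-study therapy is recorded. BP is a weak example, and the point rests on laboratory and ECG findings.
- **That the absence of a laboratory shift table is itself a gap.** Such tables belong to the statistical analysis plan, which is not shown.

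What the reply does not remove is the definition. An article may leave detail to a fuller document, but here it states a rule, and the rule as worded is too narrow for the outcome that it feeds.

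**Conclusion.** The concern holds as a defect of wording with a real consequence for the safety outcome. The stated definition, applied literally, leaves symptom-free but clinically significant laboratory and ECG abnormalities out of the only listed safety measure, and none of the tests concerned appears in another listed outcome. The likely effects are an undercount of adverse events and inconsistent recording across the seven centers.

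The size cannot be derived: the documents give no rate for such abnormalities and no indication of how often investigators would record them anyway. These tests have only one scheduled measurement after dosing, at day 90, which limits what could be found. The primary outcome, its test and the sample size are not affected.

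The conclusion assumes that the quoted sentence is the operative rule. If the full protocol carries a wider definition, the remaining task is to bring the published text into line with it.

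**What to change.** 1. Reword the definition in section {22}: any untoward medical occurrence after first dosing, including a new or worsened laboratory or ECG finding that the blinded investigator judges clinically significant, whether or not it causes symptoms. State that serious adverse events are a subset of adverse events so defined.
2. State how day 90 laboratory and ECG results feed into adverse-event recording. Have investigators apply the rule, still blinded, to the results already collected, before unblinding and database lock.
3. Report a between-arm table of shifts from baseline to day 90 in these tests, so that a difference is visible even where judgments of clinical significance vary between centers.

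**Cost.** No new measurement is needed. The work is more than a change of one sentence, because all 120 participants had been recruited by September 2021 and follow-up was due to end in December 2021. It takes an ethics-approved amendment, as {25} requires, and a blinded retrospective review of day 90 results. Adverse-event counts will rise slightly in both arms. Section {20c} leaves room for this, since it settles the final protocol and analysis before the database is locked.
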